#### Sample size and statistical analysis

We assumed that the overall mortality at 30 days is 40%
[28,29]. A sample size was calculated to detect a 10% difference in mortality at day 30 between the two groups with a two-tailed test, a significance level of 5% and a power of 80%. We plan to include a total of 708 subjects.

Baseline characteristics will be reported. The difference in 30-day mortality between the two groups will be tested using a chi-square test and intention-to-treat (ITT) analysis. Time-to-event variables including length of stay in the ICU, duration of mechanical ventilation and 30-day survival are compared between the two groups using a log-rank test. Multivariate analysis (the Cox proportional hazards regression model) is used to estimate the hazard ratio adjusted for age, severity of illness and disease category. Age and the APACHE II score will be managed as continuous variables. Adverse events will be reported according to the ITT protocol. All tests are two sided and *P*<0.05 is considered to be statistically significant. Statistical analysis will be performed using Stata 11.0 (College Station, TX 77845, USA).

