## Methods

The study is designed as a prospective randomized controlled multi-center trial in the ICUs of four tertiary academic centers. These are mixed ICUs treating both surgical and medical patients. The total number of beds is 96. The study will last for a period of 2 years. The end of the study is defined by the last follow-up of the last enrolled patient. The study was approved by the ethics committees of the participating institutions.

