#### Study end point

The primary endpoint is 30-day mortality (death from any cause before day 30).

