#### Randomization

Eligible consecutive patients will be randomly assigned to one of the treatment groups using randomization sequences generated by computer and stratified according to the primary diagnostic category on admission, namely, septic shock and ARDS. Allocation concealment is achieved using sequentially numbered, sealed opaque envelopes.

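### The primary mortality test is an unadjusted chi-square; adding the randomisation stratum, age and APACHE II, already planned as Cox covariates, would raise power at the same sample size

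*Protocol article*

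**What the plan says.** The section on sample size and statistical analysis fixes the primary test: "The difference in 30-day mortality between the two groups will be tested using a chi-square test and intention-to-treat (ITT) analysis". No stratum or covariate enters it.

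The Randomization section says that allocation is "stratified according to the primary diagnostic category on admission, namely, septic shock and ARDS".

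The analysis section also plans a Cox model, which "is used to estimate the hazard ratio adjusted for age, severity of illness and disease category", with age and APACHE II kept continuous. That model yields a hazard ratio and is not designated primary.

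On sample size the same section states: "A sample size was calculated to detect a 10% difference in mortality at day 30 between the two groups". It assumes 40% mortality, a two-sided 5% level and 80% power, and arrives at 708 patients.

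**The concern.** The plan treats diagnosis as important enough to stratify on, and age and APACHE II as important enough to adjust for. It then leaves all three out of the test that decides the trial. If baseline variables predict death, an analysis that conditions on them has more power for the same number of patients.

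The sample size leaves no reserve: 708 is exactly what the crude test needs, with nothing added for losses. At stake are a few points of power, possibly more, in a trial whose planned risk of missing a true 10-point difference is one in five. This is not a detail left to a separate analysis plan, because the article names the primary test and the covariates itself.

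**Working it through.** **Inputs from the protocol article:** 40% mortality, 10-point difference, two-sided 5%, 80% power, N = 708. **Assumed:** 1:1 allocation (354 per arm), and 40% read as the control rate, because that reading reproduces 708.

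**1. The plan's own figure.** Per arm, with unpooled variance:

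n = (1.960 + 0.842)² × (0.40×0.60 + 0.30×0.70) / 0.10² = 7.849 × 0.45 / 0.01 = 353.2, so 354 per arm and 708 in total.

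The pooled-variance formula gives 712. Other readings do not fit: 45% versus 35% gives 746 (unpooled) or 752 (pooled), and 40% versus 50% gives 770 or 776.

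**2. Power of the planned chi-square at 354 per arm.**

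z = (0.10×√354 − 1.960×√(2×0.35×0.65)) / √0.45 = (1.881 − 1.322) / 0.671 = 0.834, so power is 79.8%. The stated 80% is delivered.

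**3. Power with adjustment, by simulation.** There were 4,000 trials per setting, with N = 708, balanced allocation within two equal strata, four centres, and overall mortality of 40% versus 30%. One normally distributed score stood for age plus APACHE II. The logistic model contained arm, stratum, centre and score, and the test was on the arm coefficient. The Monte Carlo standard error is about 0.6 points per figure.

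| Assumed AUC of the score | Chi-square | Adjusted |
|---|---|---|
| 0.50 (no information) | 79.3% | 79.2% |
| 0.63 | 80.3% | 82.4% |
| 0.70 | 79.5% | 84.8% |
| 0.76 | 81.7% | 87.4% |
| 0.81 | 79.4% | 90.8% |

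A separate simulation of 3,000 trials per setting, adjusting for the score only, gave 84.0%, 87.1% and 87.8% at AUC 0.69, 0.74 and 0.78. Taken together, an AUC of about 0.63 to 0.78 gives about 82% to 89%.

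**4. The same gain in patients.** The ratio is (1.960 + z for the new power)² / (1.960 + 0.842)².

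- 82%: (1.960 + 0.915)² / 7.85 = 8.27 / 7.85 = 1.05.
- 89%: (1.960 + 1.227)² / 7.85 = 10.16 / 7.85 = 1.29.

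So the gain equals a crude analysis in about 5% to 29% more patients.

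**5. Where the gain comes from.** With a stratum odds ratio of 2 and centre log-odds effects of up to ±0.4, adjusting for stratum and centre without the score moved power from 80.5% to 81.0%. With balanced strata at 50% and 30% control mortality, a Mantel-Haenszel test over stratum gave 81.6% against 80.6% for the chi-square (200,000 simulated trials). At 45% and 35% it gave 80.4% against 80.1%. Nearly all of the gain is from age and APACHE II.

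**6. Validity.** Under no treatment effect, the simulated type I error was 5.2% for the chi-square and 5.1% to 5.4% for the adjusted models.

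**The case against.** The strongest reply is that nothing here is wrong. A chi-square test on a binary ITT endpoint is valid, simple and matched to the sample size, and it has its stated level and power. An adjusted analysis is already in the plan. The size of the gain rests on a prognostic strength that the documents do not give, and with an uninformative score there is no gain. All of this stands, and it limits the point to efficiency.

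Three stronger readings are tempting, and the documents support none of them.

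- **The crude test has the wrong level for a stratified design.** If equal strata had 50% and 30% mortality, the average within-stratum variance would be (0.25 + 0.21)/2 = 0.23, against 0.24 overall. The ratio is 0.958, which implies a true level of about 4.5%. That needs both a 20-point gap between strata and enforced balance of the arms within them. The article reports no such gap, and its Randomization section mentions no blocks. In simulation the level was 5.0% to 5.1% without enforced balance, and 4.9% to 5.0% with strata at 45% and 35%. Even the extreme case errs on the conservative side.
- **Leaving out centre is a defect.** Centre is not a stated stratification factor, a condensed article may leave its handling to the full protocol, and it adds almost no power.
- **A disagreeing Cox result would leave the conclusion open.** The article ties one test to the primary endpoint, and the Cox model estimates a different quantity. Disagreement also remains possible after the change proposed here.

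Adjustment is also not wholly free. The logistic odds ratio is conditional, while the trial was sized on an absolute difference. Patients with a missing APACHE II score would drop out of the model unless a rule prevents it.

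**Conclusion.** The point holds as lost efficiency. The planned chi-square is valid and gives about 80% power at 708 patients. Adjusting for stratum, age and APACHE II at the same sample size would give about 82% to 89%.

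The direction is secure whenever the covariates predict death, and an uninformative score costs essentially nothing (79.2% against 79.3%). The size is not secure. It assumes an AUC of about 0.63 to 0.78 and a score whose effect is linear on the logit scale, as simulated. The stratum belongs in the model because the design used it, not because it buys power.

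**What to change.** State one pre-specified ITT primary analysis: logistic regression of 30-day death on arm, the stratum recorded at randomisation, age and APACHE II (both continuous). Report the standardised absolute risk difference from that model with its 95% CI, which keeps the 10-point scale of the sample size. Say which statistic decides; the power figures above are for the test of the arm coefficient. Centre may be added but need not be. Keep the crude chi-square as a supportive analysis.

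Add a simple rule for missing baseline covariates so that no randomised patient is dropped, for example the overall mean with a missing-value indicator, applied without regard to arm.

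The cost is a change of wording, one standardisation step, and an odds ratio that must be labelled as conditional. No patients, visits or data are added. The change has to be fixed and dated before anyone deciding on it has seen outcomes by arm. This matters because the trial is already recruiting and an interim look is planned at 350 patients.

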### Patient selection

All patients admitted to a participating ICU during the study period will be assessed for potential eligibility. Patients with septic shock, ARDS or both are considered to be eligible. Sepsis is defined as infection plus systemic inflammatory response syndrome (SIRS). General variables are: (1) fever (>38.3°C) or hypothermia (core temperature <36°C); (2) heart rate >90 min^-1^ or >2SD above the normal value for age; (3) tachypnea; (4) altered mental state; (5) significant edema or positive fluid balance (>20 ml.kg^-1^ over 24 hrs); and (6) hyperglycemia (plasma glucose>140 mg.dl^-1^ in the absence of diabetes). Inflammatory variables are: (1) leukocytosis (white blood cell (WBC) count >12000 μL^-1^) or leucopenia (WBC count <4000 μL^-1^); (2) normal WBC count with >10% immature forms; (3) plasma C-reactive protein >2SD above upper normal limit; and (4) plasma procalcitonin >2SD above upper normal limit. Septic shock is defined as a systolic blood pressure (SBP) of <90 mm Hg or mean arterial pressure <70 mm Hg or a SBP decrease >40 mm Hg despite adequate fluid resuscitation
[16]. ARDS is defined according to the Berlin definition
[17]: (1) the onset should be within one week of a known clinical insult or new/worsening respiratory symptoms; (2) chest imaging shows bilateral opacities that cannot be fully explained by effusions, lobar/lung collapse or nodules; (3) respiratory failure is not fully explained by cardiac failure or fluid overload. An objective assessment may be needed to exclude hydrostatic edema if no risk factor is present. ARDS is divided into three mutually exclusive categories of mild (200<PaO_2_/FiO_2_≤300 with positive end-expiratory pressure (PEEP) or continuous positive airway pressure (CPAP)≥5 cmH_2_O), moderate (100<PaO_2_/FiO_2_≤200 with PEEP ≥5 cmH_2_O) and severe (PaO_2_/FiO_2_≤100 with PEEP ≥5 cmH_2_O). The diagnosis of ARDS is made by a specialist. Chest imaging (for example a chest X-ray or computer tomography) is interpreted by a radiologist. Patients are excluded if they met the exclusion criteria: (1) younger than 18 years; (2) experienced hemorrhagic shock; (3) are moribund, or informed consent cannot be obtained; (4) contraindications to catheter insertion, including overlying infection and arterial grafting; (5) conditions likely to render PiCCO measurements inaccurate, including intracardiac shunts, significant tricuspid regurgitation, and cooling or rewarming
[18-20].

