### Interventions

#### Experimental intervention

The PiCCO system is used within 2 hours of enrollment. Central venous access is created for the injection of cold water and measurement of central venous pressure (CVP). The choice of type of central venous catheter (CVC) and insertion site are at the discretion of the treating physician. The preferred insertion site is the jugular or subclavian position. We choose the femoral position only when both of these sites are contraindicated. A thermistor-tipped arterial catheter is inserted into the femoral artery. Occasionally, the axillary artery is used when femoral artery catheterization is contraindicated
[21]. Then 15 to 20 ml of normal saline at a temperature <8°C is injected into the central vein, and various hemodynamic parameters can be obtained through analysis of variations in blood temperature taken by the temperature sensor of the arterial catheter. At least three cold boluses are required for each calibration to obtain an acceptable precision
[22]. The calibration should be performed at least every 8 hours, or following a major change in a patient’s clinical condition
[23]. To exclude variations in blood volume and temperature caused by continuous renal replacement therapy (CRRT), the calibration will not be performed immediately after CRRT is switched on or off, and the measurement can be performed after the blood temperature reaches a steady state (after two minutes)
[24,25].

Fluid management aims to optimize the effective circulating blood volume; vasoactive agents are used to achieve a mean arterial pressure of at least 60 mmHg when the volume status is optimal and extravascular lung water is optimized to a negative fluid balance

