#### Control intervention

Patients in the control arm will not receive PiCCO monitoring, but a central venous catheter is routinely inserted. If the CVP is less than 8 mmHg, a 500 ml bolus of hydroxyethyl starch 130/0.4 (Voluven®) is infused over 30 min aiming to give a CVP of 8 to 12 mmHg. The bolus can be repeated if the target is not reached. If the CVP exceeds 12 mmHg, furosemide and/or nitroglycerin and/or dobutamine are used at the discretion of the attending physician. If MAP is less than 60 mmHg, norepinephrine is started at 0.05 μg.kg^-1^.min^-1^ with the option to increase at an increment of 0.05 μg.kg^-1^.min^-1^. If MAP > 100 mmHg, nitroglycerin is given at the dose range of 0.5 to 3.0 μg.kg^-1^.min^-1^. An RBC transfusion is triggered when Hb<7 g.dl^-1^. ScvO_2_ is maintained >70% (Figure
2).

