#### Data safety monitoring board

A Data Safety Monitoring Board chaired by the director of the Department of Critical Care Medicine (XX) of Jinhua Municipal Central Hospital, comprising experts in clinical trials, biostatistics and intensive care, has been established. The board will review data on patient characteristics, compliance and study outcome in an interim analysis (based on the availability of primary outcomes for 350 patients). The study will be terminated if one arm turns out to be harmful compared to the other.

Adverse events were considered to be: hematoma, pneumothorax, arterial emboli, catheter-relatedbloodstream infection, hemorrhage, pseudoaneurysm or arrhythmia.

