#### Ethical aspects

The study has been approved by the ethics committees of Jinhua Municipal Central Hospital, the Traditional Chinese Medical Hospital of Jinhua City, Dongyang People’s Hospital and the First People’s Hospital of Yongkang City. The research will be explained in detail to the patient or the next-of-kin prior to enrollment. The explanation will include the type and method of the study, the complications of PiCCO monitoring and the potential benefit or harm of the intervention. Written informed consent will be obtained from the patients or their surrogates. The patient or surrogate can withdraw from the study at any time.

The study is conducted according to the Declaration of Helsinki.

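### Adverse events are to be reported by allocated arm, which can understate harm from the PiCCO arterial catheter if adherence is incomplete; a supplementary table by device exposure is a cheap improvement

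*Protocol article*

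**What the plan says.** The section on sample size and statistical analysis sets the rule for safety in one sentence: "Adverse events will be reported according to the ITT protocol". No other adverse event analysis is named in the article.

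The Data safety monitoring board section lists what counts: "Adverse events were considered to be: hematoma, pneumothorax, arterial emboli, catheter-relatedbloodstream infection, hemorrhage, pseudoaneurysm or arrhythmia".

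On exposure, the Experimental intervention section says "The PiCCO system is used within 2 hours of enrollment" and "A thermistor-tipped arterial catheter is inserted into the femoral artery", with the axillary artery as an occasional alternative. The same section has the system taken out after 48 hours of clinical stability and caps its use at 10 days. The Control intervention section says "Patients in the control arm will not receive PiCCO monitoring, but a central venous catheter is routinely inserted".

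Patient selection excludes patients with "contraindications to catheter insertion, including overlying infection and arterial grafting". The Ethical aspects section notes that "The patient or surrogate can withdraw from the study at any time", and the Data safety monitoring board section says "The board will review data on patient characteristics, compliance and study outcome in an interim analysis".

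**The concern.** Analysis by allocation preserves the randomised comparison. When adherence is incomplete it usually draws the two arms together. For efficacy that is the cautious direction. For complications of a device it is the reassuring direction.

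Arterial emboli, pseudoaneurysm and access-site bleeding follow largely from placing the thermistor catheter in an artery. A PiCCO-arm patient in whom insertion is never attempted adds to the denominator without carrying that risk. A control patient who is given PiCCO carries the risk, but any complication is counted under control.

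This matters because the Discussion describes arterial access for PiCCO as safe, and readers would take the trial's safety table as a test of that statement. A clinician deciding whether to place the catheter needs the risk among patients in whom it is placed or attempted. Exposure time also varies between patients, and a rate per allocated patient does not show this.

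**Working it through.** **The plan's own figure.** The article gives no safety figure to reproduce. Its sample size does reproduce: with 40% v 30% mortality, two-sided 5%, power 80% and unpooled variance, n per arm = (1.960 + 0.842)² × (0.40 × 0.60 + 0.30 × 0.70) / 0.10² = 7.85 × 0.45 / 0.01 ≈ 353.2. This rounds up to 354 per arm, or 708 in total. It does not bear on the safety point, except that 354 per arm is used below. The allocation ratio is not stated; 1:1 is assumed.

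**Inputs.** All are assumptions, because the article states none of them:
- pd: complication rate with the PiCCO arterial catheter
- pc: complication rate without it
- a: share of the PiCCO arm with no insertion attempt
- b: share of controls who receive PiCCO

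**Formulas.**
- By-arm rate, PiCCO = (1 − a)·pd + a·pc
- By-arm rate, control = b·pd + (1 − b)·pc
- Difference = (1 − a − b)·(pd − pc)

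The retained fraction, 1 − a − b, does not depend on pd or pc. It does assume that patients who change exposure have the same underlying risk as the others.

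**Results for pd = 6%, pc = 2%.** Power is from the pooled two-proportion formula, 354 per arm, two-sided 5%.

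| a | b | PiCCO | Control | Difference (points) | Fraction kept | Power |
|---|---|---|---|---|---|---|
| 0 | 0 | 6.0% | 2.0% | 4.0 | 1.00 | 0.776 |
| 5% | 0 | 5.8% | 2.0% | 3.8 | 0.95 | 0.744 |
| 10% | 0 | 5.6% | 2.0% | 3.6 | 0.90 | 0.708 |
| 10% | 5% | 5.6% | 2.2% | 3.4 | 0.85 | 0.647 |
| 20% | 10% | 5.2% | 2.4% | 2.8 | 0.70 | 0.495 |

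Example, fourth row: 0.90 × 6% + 0.10 × 2% = 5.6%; 0.05 × 6% + 0.95 × 2% = 2.2%; 5.6 − 2.2 = 3.4 = 0.85 × 4.0.

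**Other assumed rates.** With 5% v 1% the fractions are the same. Power falls from 0.879 at full adherence to 0.770 at a = 10%, b = 5%, and to 0.618 at a = 20%, b = 10%. With 10% v 5% it falls from 0.715 to 0.581 and 0.435. The article states no powered safety hypothesis, so the retained fraction is the result to read and the power column only illustrates it.

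**Which events the formula fits.** It fits best where pd − pc comes from the arterial catheter: arterial emboli, pseudoaneurysm, and hematoma or hemorrhage at that access site. Pneumothorax, catheter-related bloodstream infection and arrhythmia can also come from the central venous catheter, which both arms have. For these pc is not small, and similar rates in the two arms would not by themselves point to dilution.

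**The case against.** **Harms by randomised arm are a legitimate report.** The trial compares two management algorithms, and reporting by arm keeps the groups comparable. This stands. It is why the by-arm table should remain the randomised comparison and not be ranked below a table by exposure.

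**The article does not exclude a further table.** A reader might infer that by-arm reporting is the sole safety analysis. The sentence does not say so, and an additional table could sit in a full protocol or analysis plan that is not at hand. What can be said is that intention to treat is the one analysis the article names for events of this kind.

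**The bias is conditional.** A reader might infer that device harm will be understated. The documents do not support that. They give no rate of non-receipt or crossover, and they limit both: patients with catheter contraindications and moribund patients are excluded, an alternative artery is available, and controls are not to receive PiCCO. The 2-hour instruction sets timing and does not show that patients miss the device. The right to withdraw does not show withdrawal before insertion. The planned compliance review shows that adherence will be looked at, not that it will be poor.

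**The events are not exclusive to the device.** A reader might also infer that the listed complications can occur only in patients who had PiCCO. The central venous catheter in both arms rules that out for several of them.

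**A table by catheter placed or not would itself hide harm.** A failed insertion can cause hematoma, hemorrhage or pseudoaneurysm, and such a split would move those events out of the PiCCO group. This is correct, and it decides how exposure must be defined.

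**Conclusion.** The point holds in a limited form. For complications that depend largely on the PiCCO arterial catheter, reporting by allocation can understate the effect of the device, by the factor (1 − a − b). The loss is nil at full adherence, 5% of the difference at a = 5% and b = 0, 15% at a = 10% and b = 5%, and 30% at a = 20% and b = 10%. None of these adherence values comes from the article, and the formula assumes that non-adherence is unrelated to complication risk. The direction is sure once there is any non-receipt or crossover and the device raises the event rate; the size is unknown.

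The stated rule is valid as far as it goes, but it does not by itself give the risk among patients exposed to the catheter. This is a cheap improvement and not a flaw that threatens the trial. The primary analysis of 30-day mortality is not affected.

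**What to change.** Keep the intention-to-treat table as the randomised safety comparison and add to the analysis section:

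1. A supplementary adverse event table by device exposure. Define exposed as PiCCO arterial catheter insertion attempted or completed, whatever the allocated arm, so that complications of failed insertion stay with the device.
2. Counts, by arm, of PiCCO patients with no insertion attempt and of controls who received PiCCO. If both are zero, the two tables coincide and the article can say so.
3. Catheter complications per exposed patient and per catheter-day. Where it can be determined, attribute each event to the arterial or the central venous catheter.
4. A note that the supplementary table is not a randomised comparison and that exposure may be related to prognosis.

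The cost is a few lines of text and one extra table. The case report form must record insertion attempts and the insertion and removal dates. The downside is a non-randomised table that could be over-read, which the note in item 4 addresses.
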